#### b- The appropriateness or inappropriateness of hospitalizations (including emergencies)

The endpoint will be the occurrence of at least one admission judged by experts as "not appropriate" or as "avoidable" in a hospital service (including emergencies) during the 18 months of follow-up (i.e. binary yes / no criterion).

Note: Only hospitalizations for which a report was available were classified by the experts.

#### c- The prevalence of psycho-behavioral disorders

|                    |                                                                   |                                                                                                            |
|--------------------|-------------------------------------------------------------------|------------------------------------------------------------------------------------------------------------|
| Principal analysis | Statistical Analysis Plan (SAP)-IDEM Study 0910701
Version 1.0 | [figure not shown]
Hôpitaux de Toulouse |
|                    |                                                                   | 07/22/2016                                                                                                 |

The endpoint will be the total score obtained in the Neuropsychiatric Inventory caregiver version (NPI) (Cummings et al., 1994, Robert et al., 1998) at the end-of-study visit (i.e., quantitative criterion).

d- The residents' process of entry into the dependency

The endpoints will be:

- the difference between the GIR scores obtained between the end-of-study visit and the inclusion visit (i.e. quantitative criterion)
- the total score obtained on the 4 items of Lawton's IADL (Lawton et al., 1969) at the end-of-study visit. This score varies between 0 and 4. (i.e. quantitative criterion).

e- The residents' quality of life

The endpoint will be the total score obtained by the QOL-AD scale (Ready et al., 2007) at the end-of-study visit (i.e. quantitative criterion).

f- The burden of the NH staff

This endpoint is collected at the level of NH centers and not at the subject level. The hardness task of caregivers will be appreciated from:

- the total number of work interruptions recorded during the 18 months of follow-up in each NH center relative to the number of beds / residents in the NH (i.e. quantitative criterion)
- the number of cumulative days of work interruptions recorded during the 18 months of follow-up in each NH center relative to the number of beds / residents in the NH (i.e. quantitative criterion)

Note 1: Only the 18-month period following the first wave of inclusion will be considered here because not all centers have achieved a second wave of inclusion.

Note 2: The number of beds / residents in each NH will be used as a measure of the number of caregivers working in each NH. Indeed, the number of NH caregivers is counted according to the number of residents / beds. Thus, the number of work interruptions in each NH will be transformed into the number of interruptions per 100 beds / residents in order to be compared between the centers.

Note 3: The turnover and the departures of the caregivers, were not collected.

g- The advanced care planning measures (advance directives ...)

|                    |                                                                   |                                                                                                            |
|--------------------|-------------------------------------------------------------------|------------------------------------------------------------------------------------------------------------|
| Principal analysis | Statistical Analysis Plan (SAP)-IDEM Study 0910701
Version 1.0 | [figure not shown]
Hôpitaux de Toulouse |
|                    |                                                                   | 07/22/2016                                                                                                 |

The endpoint will be the addition of at least one advance directive, whatever the type, in the resident's file during the 18 months of follow-up. The additions will be analyzed first globally then separately for each type of advance directive defined below.

Here are the 10 items collected in the CRF for the two intervention and control groups concerning "The planning of specific therapeutic measures" (advance directives):

- Prescriptions of therapeutic drug protocols for the management of behavioral disorders
- Requirements for non-drug therapeutic protocols for the management of behavioral disorders
- Prescriptions of therapeutic drug protocols for the management of pain
- Prescriptions of therapeutic drug protocols for the management of end-of-life discomfort symptoms (other than pain)
- Requirements for non-medical therapeutic protocols for the management of end-of-life discomfort symptoms (other than pain)
- No transfer in intensive care
- No transfer to ED
- No resuscitation
- No hospitalization
- Other

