### 6.3 Analysis of the secondary endpoints

#### 6.3.1 General

All secondary endpoints will be previously described by NH randomization group of subjects (intervention or control) and in total. The quantitative criteria will be summarized by their

|                    |                                                                   |                                                                                                            |
|--------------------|-------------------------------------------------------------------|------------------------------------------------------------------------------------------------------------|
| Principal analysis | Statistical Analysis Plan (SAP)-IDEM Study 0910701
Version 1.0 | [figure not shown]
Hôpitaux de Toulouse |
|                    |                                                                   | 07/22/2016                                                                                                 |

mean, standard deviation, median, 1st and 3rd quartile (Q1 and Q3), minimum and maximum. For the qualitative criteria, the number and percentage corresponding to each category will be presented.

All statistical tests performed to meet the secondary objectives will be bilateral with a risk of the first species at 5%. All these tests will have to be considered as purely exploratory not guaranteeing a global risk on the study of 5% (multiplicity of the tests).

The 18-month follow-up period for the secondary endpoints begins at the end of the inclusion wave in the center (i.e., the start date for the collection of judgment criteria).

Population of analysis: The analyzes on the secondary criteria of judgment will be made on the subjects of the ITT population for which the endpoint is available, except if another population is defined explicitly.

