### 6.3.8 The burden of the NH staff

This analysis will be done at the center level and not at the subject level. The total number of work interruptions and the number of cumulative days reported per 100 residents registered during the study duration in each EHPAD center will be compared between the 2 groups using a Student's test to compare the mean values (Two- Sample T-test).

Population of analysis: These analyzes will be made **on the population of randomized NHs**.

### 6.3.9 The advanced care planning measures (advance directives ...)

The presence of prescriptions in the residents' file at the end of the study will be compared between the 2 groups using a mixed model of logistic regression. The randomization group will be considered as a fixed effect and the center as a random effect.

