## 6.5 Descriptive analyzes

### 6.5.1 General

Additional descriptive analyzes will be produced on the inclusion data as well as data collected during the study that are not the endpoints. The quantitative variables will be summarized by their mean, standard deviation, median, 1st and 3rd quartile (Q1 and Q3), minimum and maximum. For qualitative variables, the number and percentage corresponding to each category will be presented.

Descriptions will be performed by randomization group of the subjects' NH and in total. The differences between the 2 groups will not be tested statistically in these descriptive analyzes.

Population of analysis: The descriptive analyzes will be done **on the subjects of the ITT population for which the data is available**, except if another population is defined explicitly.

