### 6.5.3 Description of data collected at inclusion

The characteristics found in the randomized NH centers (randomization stratification factors, number of residents included) will first be described.

The following characteristics of the subjects identified for inclusion in the study will be described for the entire analysis population and will be described in the 2 groups (intervention, control):

- Criteria for inclusion and non-inclusion;
- Sociodemographic characteristics (age, sex, marital status, education, mother tongue (French yes / no), occupation (yes / no), seniority in the NH (in months);
- Medical history and associated pathologies (visual or auditory impairment, smoking and alcohol consumption, total Charlson Comorbidity Index score);

|                    |                                                                   |                                                                                                            |
|--------------------|-------------------------------------------------------------------|------------------------------------------------------------------------------------------------------------|
| Principal analysis | Statistical Analysis Plan (SAP)-IDEM Study 0910701
Version 1.0 | [figure not shown]
Hôpitaux de Toulouse |
|                    |                                                                   | 07/22/2016                                                                                                 |

- Cognitive antecedents (progressive decline yes / no, MMSE test yes / no and score, cognitive assessments yes / no and type of assessment);
- Family history of dementia (presence of family history of dementia yes / no);
- Hospitalizations during the last 3 months by type of hospitalization (planned or in emergency) and by type of service;
- Ongoing drug and non-drug treatments at inclusion by type of treatment;
- Anticipated prescriptions by type;
- GIR total score at inclusion.

The following results from the Comprehensive Geriatric Assessment (CGA) obtained during the inclusion visit only for the intervention group, will be described:

- Overall MMSE score;
- Results of the clock test (score and normality);
- Results of the Borson Mini-Cog (normality);
- Overall score of the 5 word test;
- Categorical verbal fluency test results (total words generated, total acceptable words);
- Confusion Assessment Method (CAM) test result (acute confusional state yes / no);

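### The by-type advance-directive analyses (SAP 4.2 g and 6.3.9) ignore items already on file at inclusion, which costs precision and lets a chance baseline gap shift the odds ratio

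*SAP*

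**What the plan says.** Section 4.2 g: "The endpoint will be the addition of at least one advance directive, whatever the type, in the resident's file", counted over 18 months of follow-up. It continues: "The additions will be analyzed first globally then separately for each type of advance directive defined below". Ten items follow. Five are therapeutic protocols for behaviour, pain or end-of-life symptoms. Four limit care (intensive care, ED transfer, resuscitation, hospitalization). The last is an open *Other* item.

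Section 6.3.9, the only analysis text for this endpoint, names a different outcome: "The presence of prescriptions in the residents' file at the end of the study will be compared between the 2 groups". The model is a mixed logistic regression: "The randomization group will be considered as a fixed effect and the center as a random effect". It has no other term.

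Section 6.3.1 sets the analysis set for secondary endpoints: "ITT population for which the endpoint is available, except if another population is defined explicitly". No other population is defined for directives.

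Section 6.5.3 lists, among the inclusion data described in both groups, "Anticipated prescriptions by type". Under 6.5.1 this is descriptive only: "The differences between the 2 groups will not be tested statistically in these descriptive analyzes". Section 6.3.6, by contrast, adjusts the change in GIR score for its inclusion value.

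**The concern.** For a by-type addition, a resident who has the item at inclusion has nothing left to add. The plan has no at-risk set and no baseline term, so this resident stays in the model and carries no information about the intervention. If many residents hold an item, the comparison loses precision. If the arms happen to differ in how many hold it, the difference enters the odds ratio.

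The by-type results are where care-limiting directives can be told apart from symptom protocols. One of the items, no transfer to the ED, bears directly on the primary endpoint. The baseline data needed to deal with this are already collected in both arms.

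**Working it through.** **Inputs.** The SAP gives no rate, baseline share or power for this endpoint, so there is no figure to reproduce. From section 3.3 I take 1,000 residents per arm, 30 per home, 35 homes per arm and ICC 0.02. The design effect is 1 + 29 × 0.02 = 1.58, and the effective size is 1,000/1.58 = 633 per arm. The assumed values are new entry p of 20% (control) and 30% (intervention) among residents without the item, and a share b holding it at inclusion.

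**Formulas.**
- Addition, holders coded No: (1 − b)p.
- Presence at end, holders keep the item: b + (1 − b)p.
- At risk only: p, on 633(1 − b) per arm.

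Example at b = 40%: addition is 0.6 × 20% = 12% versus 0.6 × 30% = 18%, odds ratio (OR) (0.18/0.82)/(0.12/0.88) = 1.61. Presence is 52% versus 58%, OR 1.27. At risk is 20% versus 30%, OR 1.71.

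**Equal baseline in both arms** (OR, power):

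| b | At risk only | Addition, all residents | Presence, all residents |
|---|---|---|---|
| 20% | 1.71, 95.8% | 1.66, 94.6% | 1.40, 82.8% |
| 40% | 1.71, 89.1% | 1.61, 84.9% | 1.27, 57.4% |
| 60% | 1.71, 74.0% | 1.57, 66.0% | 1.21, 34.2% |

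For addition the loss is small. The risk ratio stays at 1.50 throughout. For unadjusted presence the loss is large.

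**Unequal baseline, no true effect** (p = 20% in both arms):

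| Holders, intervention / control | Addition | OR | Presence | OR |
|---|---|---|---|---|
| 20% / 30% | 16% v 14% | 1.17 | 36% v 44% | 0.72 |
| 40% / 20% | 12% v 16% | 0.72 | 52% v 36% | 1.93 |

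The two outcomes move in opposite directions.

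**How often this matters.** I simulated 35 homes per arm with 30 residents each, no effect, mean holding 30% and home-level ICC of holding from 0.02 to 0.5. A cluster-level t-test stood in for the mixed model. Over all randomisations the type I error is 4.9% to 5.3% for both outcomes. The baseline gap between arms stays below 5.0 points in 95% of trials at ICC 0.02, below 12.3 at ICC 0.3 and below 15.4 at ICC 0.5. The 40%/20% row is therefore an extreme case. At ICC 0.3, among trials with a gap above 10 points, false rejections are about 21% for addition and 44% for presence.

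**Holding concentrated in some homes.** All inputs here are assumed: 44 homes per arm, 24 residents each, ICC 0.05, 25% versus 15% additions among those without the item, 90% holding in homes where the item is policy and 10% elsewhere.
- 20% policy homes: b = 0.2 × 90% + 0.8 × 10% = 26%. Additions are 18.5% v 11.1%, OR 1.82 against 1.89 at risk. Simulated power is 81–85% on all residents and 93% at risk.
- 40% policy homes: b = 42%. Additions are 14.5% v 8.7%, OR 1.78. Power is 61–66% against 86–88%.
- No policy homes: the loss is negligible (97% against 98%).

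**The case against.** Four points on the other side have force.

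- **Coding.** A reader might infer that the plan counts existing holders as No. It has no such rule. The availability condition in 6.3.1 could be read to leave holders out, and 6.3.9 would count a retained item as Yes. This stands. No is the natural value under 4.2 g, but it is an inference, and the choice of outcome comes first.
- **Structural zeros.** A reader might infer that none of the ten items can be added twice. The five protocol items are worded in the plural and *Other* is open, so a second entry might count as an addition. The case report form is not shown. The zero is certain only for the four care-limiting items, and a blanket filter could discard genuine additions.
- **Bias.** A reader might infer that home policy will systematically pass for an intervention effect. Homes are randomised and the model handles clustering, so the error rate over all randomisations stays near 5%. What remains is lost precision, and bias conditional on a chance gap. The inclusion table would show that gap but would not correct the estimate.
- **Policy homes.** Nothing in the SAP says that homes apply an item to most of their residents. The larger power losses for addition rest on that assumption.

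None of this removes the core point. Baseline holding matters under either outcome, and the plan uses it under neither. The global endpoint of 4.2 g is less exposed under addition, since a holder of one type can still add another.

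**Conclusion.** The point holds, and it is minor. The by-type analyses have neither an at-risk set nor a baseline term, although holdings by type are recorded at inclusion in both arms.

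Under addition, on the assumed rates with evenly spread holding, power falls by about 1 point with 20% holders, 4 points with 40% and 8 points with 60%, and the odds ratio barely moves. Losses of 20 points or more need holding to be concentrated in 40% of homes, which is an assumption. Under unadjusted presence the loss is much larger: 57.4% power at 40% holders against 89.1% at risk. That figure assumes that items on file are kept.

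The documents do not support a claim of systematic bias or of an inflated overall error rate. Section 6.3.1 declares all secondary tests exploratory, so no confirmatory conclusion depends on this.

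**What to change.** Choose one outcome and state it identically in 4.2 g and 6.3.9.

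- **If addition:** analyse each care-limiting item in ITT residents without that item on file at inclusion, and show the number at risk by arm. For the protocol items and *Other*, where a further entry may count as an addition, keep all residents and add baseline holding of that item as a fixed covariate. State whether a second protocol of the same type counts.
- **If presence:** add baseline holding of that item as a fixed covariate for every type.

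In either case, say what happens if nearly all holders have the same outcome. The covariate then separates the data and the model may not converge. Restricting to residents without the item is the obvious fallback.

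The cost is SAP wording plus a filter or a covariate on data already collected in both arms. The downside is that the restricted models have fewer residents and the analysis set differs by type, so each by-type result needs its own denominator.

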#### 4.3 Additional endpoints

The following additional criteria for judgment have been added:

- the occurrence of at least one admission (planned or via ED) in any hospital service during the 18-month follow-up period (i.e. binary yes / no criterion).
- the occurrence of at least one planned admission to any hospital service except ED during the 18-month follow-up period (i.e., yes / no binary criterion).
- the occurrence of at least one emergency admission in an out-of-emergency hospital service during the 18-month follow-up period (i.e. binary yes / no criterion).

|                    |                                                                   |                                                                                                            |
|--------------------|-------------------------------------------------------------------|------------------------------------------------------------------------------------------------------------|
| Principal analysis | Statistical Analysis Plan (SAP)-IDEM Study 0910701
Version 1.0 | [figure not shown]
Hôpitaux de Toulouse |
|                    |                                                                   | 07/22/2016                                                                                                 |

## 5 STUDY POPULATIONS

### 5.1 Intention to treat population (ITT)

The ITT population will consist of all subjects included in the study who have at least 1 month of follow-up. That is, all residents of the randomized NH centers who performed the inclusion visit and who did not leave the study within one month of the start of the follow-up (i.e. the end of the inclusion period in the center).

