## 4 EVALUATION CRITERIA

### 4.1 Primary endpoint

The primary endpoint of this study, collected by subject, will be the occurrence of at least one admission to a hospital ED during a one-year follow-up period (i.e., yes / no binary criterion).

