## 6 STATISTICAL ANALYZES

### 6.1 Principal analysis of the primary endpoint

The number and percentage of subjects who had at least one admission to a hospital ED in a one-year follow-up period will first be described by randomization group of the patient's NH (intervention or control) and in total.

The 1-year follow-up period for each subject begins at the end of the wave of inclusion in the center (i.e. start date of hospitalization collection).

The primary analysis of the effectiveness of management will compare the ED transfer rate between the two groups after a 1-year follow-up. To account for intra-center correlation (i.e., non-independence between observations of the same center) the effect of the intervention will be tested using a logistic regression model with random effects. The center randomization group (i.e. NH) subjects will be considered as a fixed effect and the center as a random effect

|                    |                                                                   |                                                                                                            |
|--------------------|-------------------------------------------------------------------|------------------------------------------------------------------------------------------------------------|
| Principal analysis | Statistical Analysis Plan (SAP)-IDEM Study 0910701
Version 1.0 | [figure not shown]
Hôpitaux de Toulouse |
|                    |                                                                   | 07/22/2016                                                                                                 |

to model the risk of a transfer to the ED. The risk of the first species for this main analysis is set at 5% (confirmatory test).

The intra-class correlation coefficient will also be calculated from this model.

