Population of analysis: The main analysis of the primary efficacy endpoint of the intervention will be carried out on the subjects of the ITT population. Thus, subjects who left the study before 1 year of follow-up will still be considered in this analysis if their follow-up is at least 1 month. For example, a patient who died after 4 months of follow-up without ED transfer will have a primary endpoint equal to "No". This will lead to a possible underestimation of the rates of subjects admitted to ED in 1 year in the 2 groups but should not bias the comparison between the groups since the follow-up times should be close between the 2 groups.

As sensitivity analyzes, this analysis will also be performed on the PP1 population in addition to the ITT analysis.

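### The set labelled ITT for the confirmatory test is a modified ITT: residents who leave in the first month of follow-up are removed, together with any emergency transfer already recorded for them

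*SAP*

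**What the plan says.** SAP Section 5.1 defines the set: "The ITT population will consist of all subjects included in the study who have at least 1 month of follow-up". It then spells the rule out as residents of randomised homes "who performed the inclusion visit and who did not leave the study within one month of the start of the follow-up". The reason for leaving and any ED transfer before leaving play no part.

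Section 6.1 makes this the set for the confirmatory 5% test: "The main analysis of the primary efficacy endpoint of the intervention will be carried out on the subjects of the ITT population". It repeats the condition for those who leave before one year, who "will still be considered in this analysis if their follow-up is at least 1 month".

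The endpoint in Section 4.1 is "the occurrence of at least one admission to a hospital ED during a one-year follow-up period", as a yes/no variable. Section 6.1 says that each resident's year "begins at the end of the wave of inclusion in the center (i.e. start date of hospitalization collection"). Follow-up and the recording of transfers therefore begin on the same day.

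Section 6.1 also shows how later leavers are coded: a resident who dies at four months without a transfer counts as No. The SAP gives no reason for the one-month minimum.

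**The concern.** Homes are randomised, so whether a resident stays for one month is known only after randomisation. It is also known only after contact that differs by arm: under the SAP summary (inclusion and follow-up) and Section 6.5.3, only intervention residents have the comprehensive geriatric assessment at the inclusion visit. A filter applied at that point can select differently in the two arms, and intention-to-treat analysis exists to prevent this.

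The filter also conflicts with the SAP's own coding. A resident transferred on day 10 who dies on day 20 has a known Yes inside the endpoint window and is removed. A resident who leaves on day 40 without a transfer stays in as No. Because leavers are coded by observed status, the endpoint needs no minimum follow-up.

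At stake are the label under which the main result is reported and a small number of true primary events.

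**Working it through.** **1. Which residents lose a known event.**
- Left before follow-up start, during the inclusion wave: excluded, but no ED data are collected for them, so no known event is lost.
- Left in days 0 to 30: excluded although transfers were being recorded. Any recorded Yes is discarded.
- Left after one month: kept, coded by observed status.

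Only the second group carries the loss of known events.

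**2. Whether another analysis restores them.**
- PP1 and PP2 (Sections 5.2 and 5.3) are subsets of the ITT set.
- The only 1-year sensitivity analysis (Section 6.6) uses PP1.
- The adjusted model, the incidence rates and the competing-risk analysis (Section 6.2) use the ITT set, with PP1 added for the rates.
- The 18-month analyses (Section 6.3.2) use ITT, PP1 and PP2.

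None brings these residents back.

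**3. The plan's own figures.** The SAP gives no figure for the one-month exclusion. Its planning rates (Section 3.3) are 24% and 24% × 0.7 = 16.8%. The standard two-proportion formula (two-sided 5%, 80% power) gives 491 per group, or 518 with continuity correction, against the SAP's 516. The rates are therefore a sound basis. With 1,000 per group, expected events are 240 + 168 = 408.

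**4. Residents removed.** Input: 20% yearly attrition, described in Section 3.3 as REHPA deaths. Assumption: spread evenly over the year.
- Linear: 0.20 / 12 = 1.67% per month; × 2,000 = 33.
- Constant hazard: 1 − 0.8^(1/12) = 1.84% per month; × 2,000 = 37, or 18.4 per arm.

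**5. Events lost.** Events lost = residents removed × share with a prior ED transfer. The share is assumed. With 36.8 removed, 10% gives 3.7 and 50% gives 18.4, so about 4 to 18 of 408.

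**6. Effect on one arm's rate.** For a true 24% in 1,000, the analysed rate is (240 − 18.4 × share) / (1,000 − 18.4):

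| Share with prior ED transfer | Events lost per arm | Analysed rate |
|---|---|---|
| 10% | 1.8 | 24.3% |
| 25% | 4.6 | 24.0% |
| 50% | 9.2 | 23.5% |
| 80% | 14.7 | 23.0% |

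**7. Effect on the comparison, equal loss in both arms.** Remove 18 residents with 9 events from each arm: 231/982 = 23.5% against 159/982 = 16.2%, relative risk 0.69 instead of 0.70. With 2 events per arm: 238/982 against 166/982, relative risk 0.70.

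**8. Effect on the comparison, unequal loss and no true effect.** Both arms truly 24%. Remove 20 residents with 10 events from each arm: 230/980 = 23.5%. Then remove 10 more, each with an event, from one arm only: 220/970 = 22.7%. The spurious relative risk is 0.97. With 15 more it is 215/965 = 22.3%, relative risk 0.95. These are deliberately strong imbalances against the 17 to 18 leavers per arm expected in step 4.

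**The case against.** The best defence is that the rule is prespecified, identical in both arms and triggered by leaving the study, not by an ED transfer. A resident transferred on day 10 who stays in the study is counted. With balanced losses the relative risk moves by about 0.01. All of this stands. It limits the size of the problem but does not make the set intention-to-treat.

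The count may also be too high. The 20% is an average for REHPA residents, whereas this trial requires a life expectancy above one year and excludes bedridden residents, so first-month deaths may be fewer than an even spread implies. Departures for other reasons would add to the count. The 33 to 37 is an order of magnitude.

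The SAP does address bias, but its reassurance in Section 6.1 concerns shorter follow-up among residents who are kept. Section 6.5.7 will tabulate dropouts by group with reasons, but its first time band is under three months and Section 6.5.1 makes the ITT set the default population, so first-month leavers may be neither separated nor included.

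Two stronger readings are tempting and are not supported:
- A reader might add the inclusion wave and compute deaths over three months: 1 − 0.8^(3/12) = 5.4%, or about 108 of 2,000. That treats every resident as included on the first day of a full two-month wave, and most of the added residents leave before ED collection begins, so no known event is lost with them.
- A reader might infer that the discarded events are those the care plan would most affect. The SAP gives no date for the first team meeting, so nothing shows that a plan was in place during days 0 to 30.

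**Conclusion.** The point holds in limited form. The confirmatory population is a modified ITT that can discard recorded primary events, and no planned resident-level comparison shows the result without the exclusion. On even attrition at the SAP's rate, and an assumed 10 to 50% of early leavers transferred first, the loss is about 4 to 18 of roughly 400 events.

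It would be wrong to infer that the trial's result is seriously biased or that power is affected. The sample size is unchanged, and a material bias needs a marked imbalance between arms in early leavers who had an event. Such an imbalance cannot be ruled out: the homes know their arm and only one arm has the assessment at inclusion. The correction is simple, so the plan should make it, but this is a should-fix and not a fatal flaw.

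**What to change.** 1. In Sections 5.1 and 6.1, drop the one-month minimum. Define the primary set as all included residents of randomised homes who were still in the study at follow-up start, analysed in their home's arm.
2. State that any ED transfer from follow-up start counts as Yes, whatever happens next. The incidence-rate and competing-risk analyses can use any follow-up time above zero.
3. Keep the set with at least one month of follow-up as a sensitivity analysis in Section 6.6, labelled as modified ITT.
4. Report by arm, with reasons, the residents who left between the inclusion visit and follow-up start. Add a sensitivity analysis that includes them coded No, and note that no ED data were collected for them.
5. In Section 6.5.7, show first-month leavers as their own category by arm, with reason and ED status, on all included residents.
6. State whether PP1 and PP2 are now drawn from the new set or keep the one-month condition.

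The cost is SAP wording and a few extra tables. Transfers are already collected from follow-up start and dropout reasons are already planned for description, so the primary analysis needs no new data and the sample size does not change. If the one-month rule comes from the protocol, which is not at hand, the change should also be listed in Section 2.
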